### Sample size

Following earlier RCTs [34] it is expected that patients in the usual care group (controls) will respond with a mean reduction in HRSD of six points. Adding exercise to usual care is expected to result in a decline of at least eight points in HRSD score (thus two extra points). To detect this difference, with an α (two-tailed) of 5% and a power (1-β) of 80%, using two equal groups and a standard deviation of 5 points, 100 patients are needed in each group. Taking 30% drop-out into account, 140 patients have to be included in each group.

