### Randomisation, blinding and treatment allocation

Randomisation takes place at every location separately. This way, every location will have an equal distribution of participants between the intervention and control group. The SPSS random generator (SPSS version 14.0) [50] will be used to allocate patients. Ten closed envelopes with allocation numbers are presented to the participants. They choose an envelope, after which the research assistant tells the patients in which arm of the study they are included. Evaluators of the main outcome measure (HRSD) are blinded for group allocation and are trained regularly for inter-rater reliability. All other measures will be evaluated by a research assistant, who is not blinded for group allocation.

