### Statistical analyses

Comparability of the intervention and control groups will be examined for the baseline measurements. If necessary, analyses will be adjusted for baseline differences. The primary analysis of the data set will be according to the 'intention to treat' principle. A secondary 'per protocol' analysis will be done taking into account the level of compliance and the amount of exercise during the intervention period. Usual daily physical activity, tobacco smoking and alcohol intake will be treated as confounders.

Differences in remission rates (and other categorical outcomes) between the experimental groups are examined by contingency table Chi-square statistics. Differences in mean scores on continuous outcomes (e.g. HRSD) between the intervention groups are examined by analysis-of-variance.

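### Allocation is done within each location, but the Chi-square named for remission takes no account of location; if remission differs between locations, it gives up some power

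*Protocol article*

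**What the plan says.** In the protocol article, the section on randomisation, blinding and treatment allocation makes location a stratum of the design: "Randomisation takes place at every location separately". It gives the purpose as well: "every location will have an equal distribution of participants between the intervention and control group".

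The Statistical analyses section names the test for remission: "Differences in remission rates (and other categorical outcomes) between the experimental groups are examined by contingency table Chi-square statistics". Location does not appear there. It is also absent from the next sentence, which assigns continuous outcomes such as HRSD to analysis-of-variance. The section offers adjustment for baseline differences only where this proves necessary, and it lists usual physical activity, smoking and alcohol as confounders.

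Remission has no stated rate and no power calculation. The primary outcome is the reduction in HRSD, and the Sample size section concerns that outcome alone.

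**The concern.** A trial that balances its arms within location normally carries location into the analysis. If remission rates vary by location, part of the variation in the pooled table lies between locations. Balanced allocation has already removed that part from the treatment comparison, but the pooled Chi-square still counts it as error. Its variance is then too large, so its error rate falls below the nominal level and it detects a real effect less often.

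The conditional adjustment clause is unlikely to repair this. A factor balanced by design should not show up as a baseline difference between arms, so looking for imbalance would not bring location in. The same holds for baseline HRSD: it is measured in every patient and could sharpen the comparison whether or not the arms happen to differ on it.

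What is at stake is precision for remission and the other categorical outcomes.

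**Working it through.** **The plan's own figure.** The Sample size section expects "a decline of at least eight points in HRSD score (thus two extra points" and concludes: "using two equal groups and a standard deviation of 5 points, 100 patients are needed in each group". With two-sided 5% and 80% power, n per arm = 2 × (1.960 + 0.842)² × 5² / 2² = 98.1, so 99; 100 per arm gives 80.7% power. The section continues: "Taking 30% drop-out into account, 140 patients have to be included in each group". Dividing by the retained fraction gives 100 / 0.70 = 143, and 140 × 0.70 = 98 completers gives 80.0% power. The HRSD figures therefore reproduce closely, but they say nothing about remission.

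**Inputs for remission.** From the article: equal arms, intended balance within location, two-sided 5%, and 140 per arm enrolled or 100 per arm for analysis. Assumed, because the article gives no values: two equal locations, mean control remission 30%, and a common odds ratio of 2. The spread between locations is varied.

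**Error rate in closed form.** Let p_s be the remission rate at location s when there is no treatment effect, and p̄ the mean of these rates. With exact balance, the ratio of the true variance to the variance used by the pooled Chi-square is

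R = mean[p_s(1 − p_s)] / [p̄(1 − p̄)],

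and the real two-sided error rate is 2 × [1 − Φ(1.96 / √R)].

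- Rates 20% and 40%: R = [(0.16 + 0.24) / 2] / 0.21 = 0.952, error rate 4.46%.
- Rates 10% and 50%: R = [(0.09 + 0.25) / 2] / 0.21 = 0.810, error rate 2.94%.

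**Simulation.** There were 200,000 trials per scenario, with arms exactly balanced within location. The Pearson Chi-square without continuity correction was compared with the Cochran-Mantel-Haenszel (CMH) test stratified by location. Treated rates follow from the odds ratio: at 10% the odds 0.111 become 0.222, a rate of 18.2%; at 50% the odds 1 become 2, a rate of 66.7%; their mean is 42.4%. Results for 140 per arm, in percent:

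| Control rates | R | Error rate, Chi-square | Error rate, CMH | Power, Chi-square | Power, CMH | Loss (points) |
|---|---|---|---|---|---|---|
| 30 / 30 | 1.000 | 5.05 | 4.95 | 80.0 | 79.8 | −0.2 |
| 25 / 35 | 0.988 | 4.89 | 4.96 | 79.2 | 79.6 | 0.4 |
| 20 / 40 | 0.952 | 4.57 | 5.09 | 76.1 | 77.5 | 1.4 |
| 15 / 45 | 0.893 | 3.83 | 4.98 | 70.4 | 74.3 | 3.9 |
| 10 / 50 | 0.810 | 2.97 | 5.02 | 60.1 | 68.9 | 8.8 |

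The simulated error rates agree closely with the closed form.

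**Sensitivity.** At 100 per arm the pattern is the same: 61.1% versus 62.8% power at 20/40, and 43.8% versus 54.2% at 10/50. Four locations at 20/25/35/40 with 140 per arm give 77.7% versus 78.6%; at 10/20/40/50 they give 68.9% versus 73.6%.

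**If balance is not enforced.** With simple randomisation inside each location, 100 per arm and rates 10/50, the Chi-square has an error rate of 5.0%. Its power is still lower, 45.0% versus 54.0%. The low error rate therefore depends on real balance, but the power loss does not.

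Baseline HRSD was not part of the simulation, so no size is attached to that half of the point.

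**The case against.** The strongest reply is that the article is a condensed account. It does not say that tables are pooled over locations, a CMH test is itself a Chi-square statistic on contingency tables, and a fuller plan may specify the strata. This stands in part: the lack of stratification is read from the ordinary meaning of the named test. Yet the article does name a test rather than leave the matter open, and nothing near it points to location.

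A reader might infer three stronger things, and the documents support none of them.

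- *That power is certainly lost.* This needs location to predict remission. The article includes both inpatients and outpatients, which may suggest that locations differ, but it does not say that the mix varies by location. Nor would stratifying by location remove differences between settings within a location.
- *That the error rate is certainly below 5%.* This needs enforced balance. Equal distribution is the stated aim, but the draw from ten envelopes is described without an explicit blocking rule. Supervised group sessions, held in the intervention arm only, could also induce correlation within groups and push the error rate upward.
- *That the remission result would be invalid.* Ignoring a prognostic stratum does not inflate false positives.

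It is also fair to say that remission is not among the listed aims, and that a Chi-square test is acceptable for a secondary comparison. That limits the importance of the point but is no reason to prefer the weaker test.

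**Conclusion.** The point holds as a conditional and minor one. The design uses location and the named test for categorical outcomes does not. Under the stated assumptions the cost runs from nothing, when locations share the same remission rate, through 1 to 2 points of power at a 20-point spread, to about 9 points at 10% versus 50% with 140 per arm. In that last case the error rate is about 3%, provided the arms are balanced within location. The number of locations, the remission rates, their spread and the odds ratio are all assumed, so the table is a range and not an estimate for this trial.

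The case for change does not depend on which row is true. When locations do not differ, the stratified test performs practically the same (79.8% against 80.0% power); when they do, it gains. The validity of the trial and its primary outcome test are not called into question by this point.

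**What to change.** In the Statistical analyses section, replace the contingency-table Chi-square for remission by either a Cochran-Mantel-Haenszel test stratified by location, or a logistic regression with arm, location and baseline HRSD. Report the adjusted odds ratio with its confidence interval, and give the crude remission proportions per arm beside it, since an adjusted odds ratio need not equal the crude one. The regression is the only one of the two that also uses baseline HRSD. For categorical outcomes with more than two levels, such as the graded pain scale, name the corresponding stratified or ordinal method.

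Include location in the HRSD analysis-of-variance as well. That analysis is equally silent on location and carries the primary outcome.

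The cost is a few sentences of text. Location has to be known for each patient in order to allocate within it, and baseline HRSD is collected from everyone, so no new data are needed.

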### Ethical principles and safety

The study has been designed and will be carried out in accordance with the principles of the Helsinki Declaration (Edinburgh, Scotland Amendment, October 2000). The study protocol has been approved by the Medical ethical committee for mental health (Metigg Kamer Noord).

## Discussion

The aim of this study is to investigate the effectiveness of aerobic exercise therapy (RT or NW) on depression in adult patients in addition to usual care. Also, the effect of physical exercise on frequently existing co-morbid diseases or risk factors for such disorders as metabolic syndrome is an objective of this study.

This is the first well conducted add-on randomised controlled high-quality trial into the effect of aerobic exercise on depression with a correct randomisation procedure, blinded outcome assessment, intention to treat analysis, study into cost-effectiveness, quality of life and long-term follow-up as was advised in earlier publications. EFFORT-D can therefore contribute to stronger evidence for this type of intervention, which can result in more specified recommendations for clinical practice. Another strength of this study is the fact that also severely clinically depressed patients, who are mostly excluded in other studies, will be included. A relatively greater effect of exercise in this subgroup of severely depressed patients is possible. A challenge of the study lies in the motivational techniques needed to exercise with depressed patients, which is proven to be difficult [52] and it will take a serious effort not to exceed the calculated 30% drop-out patients in the intervention group. Because this study is supported by a strong hypothesis and minimal negative side effects are expected, one-tailed statistical analysis is also possible if the large number of included participants can't be reached within the planned time. Furthermore, the diversity of outcome measures makes it possible to distinguish more explicitly those depressed patients that could benefit most from exercise.

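### The one-tailed fallback makes the sidedness of the primary HRSD test depend on recruitment, and at the usual 5% level it would lower the bar for claiming benefit

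*Protocol article*

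**What the plan says.** The Sample size section of the protocol article plans the trial "with an α (two-tailed) of 5% and a power (1-β) of 80" per cent, for two extra points of HRSD reduction (eight against six). It continues: "using two equal groups and a standard deviation of 5 points, 100 patients are needed in each group". It then allows for losses: "Taking 30% drop-out into account, 140 patients have to be included in each group".

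The Statistical analyses section names the method without a sidedness: "Differences in mean scores on continuous outcomes (e.g. HRSD) between the intervention groups are examined by analysis-of-variance".

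The Discussion then opens a fallback. It begins "Because this study is supported by a strong hypothesis and minimal negative side effects are expected" and concludes that "one-tailed statistical analysis is also possible if the large number of included participants can't be reached within the planned time". Nothing elsewhere in the article withdraws or limits this.

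**The concern.** Whether a test is one- or two-tailed should follow from the question and from which results would change practice. It should be fixed before the data come in. Here it is tied to how many patients enrol. Fewer patients mean less information, and the honest consequence is a wider interval. A one-tailed test at a more lenient level instead reduces the evidence needed to declare benefit.

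The option is also loosely drawn. It does not say at what level the one-tailed test would be run, how large a shortfall triggers it, or when the choice is made and by whom. The primary inference of the trial is at stake. With a shortfall, an HRSD difference that fails the planned test could be reported as significant, and a worse outcome under exercise could no longer be declared.

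**Working it through.** **Inputs.** From the Sample size section: difference δ = 8 − 6 = 2 points, SD σ = 5, equal groups, two-tailed α = 5%, power 80%, 100 evaluable and 140 included per group, drop-out 30%. From the Discussion: a one-tailed option, with no level given. *Assumption:* one-tailed 5%, with one-tailed 2.5% shown as the other end of the range.

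**1. Reproduce the plan's figure.** n per group = 2(z_α + z_β)²σ²/δ².

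- Two-tailed 5%: 2 × (1.960 + 0.842)² × 25/4 = 98.1, so 99. The t-test version gives 99.08, so 100. This agrees with the stated 100.
- Drop-out: 100/0.7 = 142.9, so 143. The stated 140 leaves 140 × 0.7 = 98 evaluable, which is close enough.

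**2. Which one-tailed level would serve the stated purpose?**

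- One-tailed 2.5% uses z = 1.960 again and needs 99 per group. It offsets no shortfall.
- One-tailed 5% uses z = 1.645: 2 × (1.645 + 0.842)² × 25/4 = 77.3, so 78 per group (t-test version 77.97), or 78/0.7 = 111.4, so 112 included.

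Only a level above 2.5% makes the fallback useful when patients are short, and 5% is the conventional one. This is an inference, not a statement in the article.

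**3. Error rates under the one-tailed 5% assumption.**

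- False claim of benefit: 1 − Φ(1.960) = 2.5% as designed, and 1 − Φ(1.645) = 5.0% once the switch is made.
- Total type I error: 2.5% + 2.5% = 5% as designed, and 5% + 0% = 5% after the switch.
- If the switch happens with probability q, independently of the results, the average false-benefit risk is 2.5% × (1 + q), for example 3.75% at q = 0.5.

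**4. Power with a shortfall.** Normal approximation: power = Φ(δ/(σ√(2/n)) − z).

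| Evaluable per group | Two-tailed 5% | One-tailed 5% |
|---|---|---|
| 100 | 80.7% | 88.2% |
| 78 | 70.5% | 80.3% |
| 70 | 65.8% | 76.5% |
| 60 | 59.1% | 70.7% |
| 50 | 51.6% | 63.9% |

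With the t-test, two-tailed power is 80.4% at 100 and 69.9% at 78, and one-tailed power at 78 is 80.0%. The 78 is an illustration, chosen as the point where one-tailed power reaches 80%. The article does not mention it. The shortfall covered is 1 − 78/99 = 21%.

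At 78 per group the smallest significant difference is z × 5 × √(2/78): 1.57 points two-tailed and 1.32 points one-tailed. An observed benefit between those two values would change from non-significant to significant because of the switch alone.

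**5. The two reasons set against the Background.** The section on scientific evidence for exercise says that results on the curative effect conflict. It reports one meta-analysis with an effect size of −0.80, one that did not support efficacy, and one with 0.40 overall but 0.19 in its three high-quality trials. The design assumes 2/5 = 0.40. This body of evidence does not settle the direction or size of the effect. Few expected side effects concern safety. They do not show that HRSD cannot be unchanged or worse with added exercise.

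**The case against.** The strongest defence is that the wording is permissive, stands in the Discussion, and is not adopted in the Statistical analyses section. The aims do state a directional hypothesis. On this view the Sample size section gives the plan for the full sample, and the Discussion only names a contingency. This stands in part: it is a badly specified fallback, and the two sections are not flatly incompatible rules. But a published option for the primary test remains available unless withdrawn, and the analysis section's silence on sidedness does nothing to close it.

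Three stronger readings are tempting, and the document does not support them.

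- *The false-positive rate simply doubles.* Only the benefit-side risk doubles, only at one-tailed 5%, and only once the switch is made.
- *The choice will be made late, with the results in view.* The stated trigger is recruitment, and no date is given. With 18 months of inclusion and follow-up to 12 months, a shortfall could be recognised before the last patients' later outcomes exist, although the earliest patients could by then have 12-month data. If the results were seen and both tests kept open, the chance of a false claim in either direction would reach 5% + 2.5% = 7.5%, but nothing says that this is intended.
- *Knowledge of allocation makes it worse.* Patients and the research assistant know the arm, but the HRSD raters are blinded, and nothing links knowing an allocation to choosing the sidedness of the test.

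**Conclusion.** The point holds in a limited form. The article plans a two-tailed 5% test and then allows sidedness to change with recruitment, without a level, threshold or date, and on reasons that its own Background does not bear out. This is a rule stated unsoundly, not a detail that could be left to an unseen analysis plan.

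Its size rests on the assumption of a one-tailed 5% level and on the switch actually being made. In that case the false-benefit risk goes from 2.5% to 5%, the bar at 78 per group falls from 1.57 to 1.32 points, and a shortfall of about 21% of evaluable patients disappears from the stated power. At one-tailed 2.5% the benefit-side error would not change, but the fallback would offset no shortfall.

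**What to change.** Delete the one-tailed option from the Discussion. State in the Statistical analyses section that the HRSD comparison is two-tailed at 5% whatever number is recruited. If recruitment falls short, report the estimated difference with its two-sided 95% confidence interval and acknowledge the reduced precision.

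The cost is one sentence removed and one added, with no extra patients or data. The real downside is that, under a shortfall, the trial must accept lower power than a one-tailed test would show, for example about 70% instead of about 80% at 78 evaluable per group.
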